### **Outcome measure**

Follow-up is set at 1, 3, 6, 12 and 24 months from initiation of treatment with the option of ending the FU at 12 months if patients is pain free with full ROM in relation to uninjured side. Elbow standard radiograph (anterior-posterior and lateral) are taken at each appointment from 3 months on until bone union is achieved or trial ends (Table 1).

Patients will be examined at the pediatric orthopedic outpatient clinic. Upon each appointment active and passive ROM of both upper limbs (elbow extension-flexion, pro-supination, wrist extension-flexion) as well as carrying angle are measured using a goniometer. Stability of both elbows are assessed using the moving valgus test and the valgus stress test. Distal sensation is examined by Semmes-Weinstein monofilaments. Signs of cold intolerance will be assessed. Grip strength is measured with a dynamometer.

Patients and guardians are requested to answer the following patient reported outcome measures at each appointment; QuickDASH, Pediatric Quality of Life InventoryTM (PedsQL), PedsQL Pediatric Pain Questionnaire, cosmetic visual analogue scale (VAS 0-100) and Mayo elbow performance score (MEPS).

Time of returning to main sport or music and its level will be documented (weeks). Any adverse effects (wound infection, nerve damage) are documented as well as hardware problems and possible hardware removal as well as conversion of treatment during FU (cast to ORIF or ligament reconstruction).

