#### **Secondary outcome:**

Difference in active ROM in comparison to uninjured arm, PedsQL, PEDS QL Pain module, Cosmetic VAS, MEPS, need for additional procedures.

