#### **Sample size**

Based on the results of Nikolas et al (2020) and Aasheim et al (2014) we assume clinically significant difference between the groups to be 6,8 and the standard deviation of the QuickDASH score to be 10

points. With 0,05 significance level and 80% power a non-inferiority comparison would require 27 patients per group. Allowing a 20% dropout rate the required sample would be 30 patients per group.

For subgroup analysis (less than 12 years vs. 12 years and over) 30 patients per age group needs to be collected. Assuming 50-50 split in the patients between the age groups the sample size would be 60 per ORIF and non-operated equaling a total of 120 patients.

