### **Statistical analysis:**

Data will be analyzed by using the Wilcoxon rank-sum test in Python 3.8. (Python Software Foundation, Wilmington, Delaware, U.S.A). Our hypothesis is that there is no difference in outcome between non-operative versus ORIF. Level of significance is set at  $p < 0.05$ .

Both treatment groups will be internally analyzed for differences in primary outcome regarding age (less than 12 years vs. 12 years and over) at time of injury and amount of initial fracture displacement (mm). Depending on group size, patient choice arm can be merged for analysis to same RCT group.

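### The rank-sum test is the only analysis the protocol names; read literally it also covers the yes/no outcome of additional procedures, where it gives no risk difference and needs a tie correction

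*Protocol*

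**What the plan says.** In the protocol, the Statistical analysis section gives one method: "Data will be analyzed by using the Wilcoxon rank-sum test in Python 3.8". The sentence is not limited to the primary outcome or to scored outcomes. No other test, effect measure or confidence interval appears anywhere in the document, and no Python library, routine or tie rule is given. The same section states the hypothesis ("Our hypothesis is that there is no difference in outcome between non-operative versus ORIF") and a significance level of 0.05, without saying whether it is one- or two-sided.

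The Secondary outcome section lists "need for additional procedures" beside the scores and range of motion. The Outcome measure section shows what would feed it: hardware problems, and "possible hardware removal as well as conversion of treatment during FU", meaning a change from cast to fixation or a ligament reconstruction. The protocol does not say whether the outcome is a yes/no per child or a count, and gives no expected rate.

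**The concern.** A rank-sum test compares orderings. When nearly every child has the same value (no further procedure), there is almost no ordering to compare, and two problems follow.

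First, the test returns a p-value but no estimate. A reader weighing surgery against a cast needs to know how many more children per hundred had another procedure, and how precisely that is known.

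Second, the textbook variance of the rank-sum statistic assumes continuous data without ties. On 0/1 data it is too large, so p-values are too large unless a tie correction is applied. In SciPy, a widely used Python library, the function that carries the test's name is ranksums. Its own documentation says that it is meant for continuous distributions and does not handle ties, and points to mannwhitneyu for tied data. An analyst who follows the sentence by name could choose ranksums, and the error would then lean towards the protocol's stated hypothesis of no difference.

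**Working it through.** **Inputs from the protocol.** 60 per arm (Sample size section), 1:1 allocation (Randomization section), significance level 0.05 (Statistical analysis section).

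**Assumptions.** Event counts and risks (the protocol gives none), two-sided testing, and SciPy as the library (version 1.17.1 was used).

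**The plan's own figure.** The protocol gives no figure for this outcome. Its 27 per group for QuickDASH reproduces with a difference of 6.8, SD 10, one-sided 0.05 and 80% power: 2 × (1.645 + 0.842)² × 10² / 6.8² = 26.7, rounded up to 27. That figure does not bear on this point.

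**Formulas.** With n per arm, N = 2n, k events in total and observed proportions p1 and p2:

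- Distance of the statistic from its null mean: U − n²/2 = n²(p1 − p2)/2
- Variance without tie correction: n²(N + 1)/12
- Variance with tie correction, for 0/1 data: (n²/12) × 3k(N − k)/(N − 1)
- Ratio of the two: (N + 1)(N − 1) / [3k(N − k)]

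**Worked case, 12/60 versus 3/60 (k = 15, N = 120).**

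- U − n²/2 = 3600 × 0.15 / 2 = 270
- Uncorrected: variance 3600 × 121 / 12 = 36,300, SD 190.5, z = 1.42, p = 0.156
- Tie-corrected: variance 300 × 3 × 15 × 105 / 119 = 11,912, SD 109.1; with SciPy's default continuity correction z = 269.5 / 109.1 = 2.47, p = 0.014
- Variance ratio: 121 × 119 / (3 × 15 × 105) = 3.05, so the uncorrected variance is about three times too large
- Fisher's exact test: p = 0.025
- Risk difference 15.0 points, Newcombe 95% interval 3.1 to 27.2

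**Other assumed counts, 60 per arm.**

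| Events | ranksums p | tie-corrected p | Fisher p | Risk difference in points (Newcombe 95%) |
|---|---|---|---|---|
| 5 vs 0 | 0.431 | 0.023 | 0.057 | 8.3 (0.7 to 18.1) |
| 8 vs 0 | 0.208 | 0.0036 | 0.0061 | 13.3 (4.5 to 24.2) |
| 10 vs 2 | 0.208 | 0.016 | 0.030 | 13.3 (2.4 to 25.0) |
| 15 vs 3 | 0.059 | 0.0023 | 0.0039 | 20.0 (7.3 to 32.7) |

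If one arm has no events, p < 0.05 needs 13 events in the other arm with ranksums, 4 with the tie-corrected form and 6 with Fisher. With 20% lost (60 × 0.8 = 48 per arm), 12 versus 3 gives 0.11, 0.012 and 0.022, so the pattern is the same.

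**Rejection rates at 60 per arm, summed exactly over all binomial outcomes.**

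| True risks | ranksums | tie-corrected | Fisher |
|---|---|---|---|
| 20% vs 5% | 16% | 73% | 63% |
| 25% vs 5% | 44% | 90% | 85% |
| 15% vs 2% | 6% | 78% | 64% |
| 5% in both arms | below 0.01% | 4.6% | 1.1% |
| 10% in both arms | 0.02% | 5.0% | 2.2% |

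**The case against.** The strongest reply has three parts.

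*The sentence is general, and a statistical analysis plan may exist.* The protocol does not write all data, it does not define this outcome as yes/no, and test choice for a secondary outcome is often left to the analysis plan. This stands in part: the mere absence of an interval or a tie rule would be no finding. But the protocol is not silent. It names one method, without limit, for data that include an outcome the method fits poorly. Correcting that scope is a fair request. Defining the outcome as a count would not help, since the values would still be mostly zero.

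*The masking depends on a routine the protocol never names.* This stands fully. A tie-corrected rank-sum test also complies with the text, and the documentation of ranksums warns against using it on tied data. The low power is a risk that the wording leaves open, not a consequence that it dictates.

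*The tie-corrected test is sound.* This also stands. At 60 per arm its actual type I error is 1.9% at a 2% risk, 4.6% at 5% and 5.0% at 10%, and at most 5.5% over risks from 0.5% to 50%. A reader might infer from 5/60 versus 0/60 (0.023 against Fisher's 0.057) that it finds significance where exact tests do not. That inference fails: Barnard's exact test gives 0.023 and Boschloo's 0.038, so the gap reflects Fisher's conservatism.

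Three other strong readings are tempting and unsupported. The routine cannot reverse the direction of a difference; it only changes whether p falls below 0.05. The documents do not rank additional procedures as the main harm, since wound infection and nerve damage are recorded too. And the option to stop follow-up at 12 months when a child has recovered says nothing about how scores are distributed, so no size can be put on any tie problem in QuickDASH.

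**Conclusion.** The point holds as a minor one. As written, the only named analysis extends to an outcome for which it gives no risk difference and no interval, and for which the p-value is far too large if the routine does not correct for ties. In the worked case that is 0.16 against 0.014 or 0.025, with power of 16% against 73% or 63% at 20% versus 5%.

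The absence of an effect estimate does not depend on the routine. The inflated p-value does, and its size rests on assumed event rates, on 60 per arm analysed and on two-sided testing. A reader might infer that the rank-sum test is invalid for this outcome; it is not, since in tie-corrected form it is close to a chi-square test (8 versus 0 events: 0.0036 against 0.0034). The primary outcome, the sample size and the data to be collected are unaffected.

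**What to change.** Change two sentences in the Statistical analysis section.

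1. Limit the rank-sum test to scores and range of motion, and require a tie-corrected or permutation form.
2. For additional procedures and any other yes/no outcome, report the proportion per arm and the risk difference (ORIF minus non-operative) with a 95% Newcombe or Miettinen-Nurminen interval as the main result. Any p-value comes from one test named in advance: a score-based or unconditional exact test that agrees with the interval, or Fisher's test with its conservatism acknowledged.

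Naming a single test matters because an interval and Fisher's p-value can disagree. For 5/60 versus 0/60 the Newcombe interval is 0.7 to 18.1 points, which excludes zero, while Fisher gives p = 0.057. Making the interval the main result settles which one is read.

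The cost is two sentences and slightly more analysis work, with no new data and no more patients. If Fisher's test is chosen, some power is lost against the tie-corrected form (63% against 73% at 20% versus 5%).

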## **METHODS AND ANALYSIS**

### **Study design:**

The study is designed as a multicenter parallel-group non-inferiority randomized controlled trial (RCT) that complies with the CONSORT guidelines (Figure 1). A patient preference arm will be available. Patient recruitment will be done at all university hospital areas of Finland (Helsinki, Kuopio, Oulu, Tampere, Turku). The study is coordinated by Helsinki University Central Hospital, Children's Hospital pediatric orthopedic unit. Trial data analysts and person performing the recruitment will be unaware of the assigned treatment.

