## **Randomization**

After agreeing to participation in the trial patients are randomized according to a computer-generated randomization list to either operative or non-operative treatment. Randomization ratio is 1:1.

Randomization is performed by the recruiting physician who is blinded to the intervention.

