#### **Primary outcome:**

Statistically significant difference in QuickDASH score is 6.8 (18) at 12 months FU.

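### The trial is declared and sized as non-inferiority, but the stated analysis is a test of no difference that never uses the 6.8-point margin

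*Protocol*

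**What the plan says.** The Protocol's Study design section describes a parallel-group non-inferiority RCT. Under Sample size, "we assume clinically significant difference between the groups to be 6,8" and "the standard deviation of the QuickDASH score to be 10" points, followed by: "With 0,05 significance level and 80% power a non-inferiority comparison would require 27 patients per group". The planned total is later raised to 60 per arm to provide for two age groups.

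The Statistical analysis section names the method: "Data will be analyzed by using the Wilcoxon rank-sum test in Python 3.8". It gives the hypothesis as "Our hypothesis is that there is no difference in outcome between non-operative versus ORIF" and sets significance at p < 0.05. It contains no margin, no interval and no rule for concluding non-inferiority.

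The Primary outcome section reads: "Statistically significant difference in QuickDASH score is 6.8 (18) at 12 months FU". So the same 6.8 is called statistically significant in one section and clinically significant in another, and a margin in neither.

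**The concern.** A non-inferiority analysis tests the null hypothesis that one arm is worse than the other by at least the margin. The unshifted rank-sum test has no difference as its null. Neither outcome of that test answers the declared question. Failing to reject is absence of evidence and leaves open a difference of 6.8 or more. Rejecting shows only that the difference is not zero, which is compatible with a difference well inside the margin.

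Because no difference is also the investigators' stated hypothesis, a non-significant result invites being reported as support for it, and a smaller or noisier trial would obtain that support more easily. The protocol also does not say which arm must be shown not worse than which. At stake is whether the primary conclusion addresses the question the trial was designed for.

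**Working it through.** **Inputs.** From Sample size: difference 6.8, SD 10, significance level 0.05 (sidedness not stated), power 80%, dropout 20%, 60 per arm planned. Completers are then 60 × 0.8 = 48 per arm. An age group of 30 per arm leaves 30 × 0.8 = 24.

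**1. Reproducing the 27.** With margin 6.8 and true difference 0:

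n = 2 × SD² × (z₁₋α + z₁₋β)² / margin²

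- One-sided 0.05: 2 × 100 × (1.645 + 0.842)² / 6.8² = 26.74, so 27. This matches the protocol.
- One-sided 0.025: 2 × 100 × (1.960 + 0.842)² / 6.8² = 33.95, so 34.
- A two-sided 0.05 test of no difference, powered for 6.8, also gives 34.

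A one-sided 0.05 test against zero with an assumed effect of 6.8 has the same algebra and would also give 27. The protocol, however, calls the comparison non-inferiority, and on that reading 27 requires 6.8 as the margin and one-sided 0.05. The Statistical analysis section does not contain that test.

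**2. True difference of 6.8.** Probability that a two-sided 5% test is non-significant (SD 10, normal data; t-test from the noncentral t distribution, Wilcoxon from 20,000 simulated trials):

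| Per arm | t-test | Wilcoxon |
|---|---|---|
| 60 (as planned) | 4% | 5% |
| 48 (60 less 20%) | 9% | 10–11% |
| 24 (age subgroup only) | 36% | 39% |

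A rule based on the upper confidence limit holds the corresponding error at about 2.5% (95% interval) or 5% (90% interval) at every size.

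**3. True difference of 3, inside the margin, 60 per arm.** The test is significant in 37% of trials (t-test) or 35% (Wilcoxon).

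**4. No true difference.** The Wilcoxon result is non-significant while the upper 95% limit still reaches 6.8 in about 29% of trials at 27 per arm, 6.5% at 48 and 2% at 60.

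**5. Is 6.8 a threshold of statistical significance?** The smallest significant mean difference (t-test) is t₀.₉₇₅ × 10 × √(2/n):

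- n = 60: 1.980 × 1.826 = 3.6
- n = 48: 1.986 × 2.041 = 4.1

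So 6.8 is not that threshold. Two examples show why the p-value does not answer the question:

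- At 48 per arm, an observed difference of 4.0 has a 95% interval of about −0.1 to 8.1. It is non-significant, yet 6.8 is not excluded.
- At 60 per arm, an observed 3.7 has an interval of about 0.1 to 7.3. It is significant, yet does not show that 6.8 was exceeded.

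**6. Power of an interval rule at true difference 0.** Φ(6.8 / (10√(2/n)) − z₁₋α):

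| Per arm | 90% interval | 95% interval |
|---|---|---|
| 60 | Φ(3.724 − 1.645) = 98% | Φ(3.724 − 1.960) = 96% |
| 48 | Φ(3.331 − 1.645) = 95% | Φ(3.331 − 1.960) = 91% |

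**The case against.** The protocol nowhere says that p ≥ 0.05 will be read as non-inferiority. The sentence on no difference may express only what the investigators expect, and it agrees with the true difference of 0 behind the 27. A rank-sum test can be run against a shifted margin, and sidedness, direction and an interval are details a statistical analysis plan often supplies. At the planned 60 per arm, the wrong reading would occur in only 4–5% of trials, about the one-sided 0.05 used for sizing.

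Much of this stands and limits the point. The error rates above describe what would follow if non-significance were taken as confirmation; they do not describe a rule the protocol adopts. The 36–39% belongs to an age-subgroup size and should not be attached to the primary comparison. Moreover, the Statistical analysis section describes the age analysis as internal to each treatment group. A reader might also take the Primary outcome wording to make 6.8 a cut-off for the observed difference, but no section proposes such a rule.

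The objection does not remove the contradiction. The protocol is not silent on the analysis: it fixes a hypothesis and a test that differ from the declared design. A later plan would have to replace that hypothesis, not merely add detail. The 4–5% is a by-product of the sample size and SD. If the SD were 15 (an assumption; the documents give only 10), the rate at 48 completers would be about 41–43%.

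**Conclusion.** Wrong as written: the design and sizing ask a non-inferiority question against 6.8, and the stated analysis tests a different hypothesis without using 6.8. A reader might infer that the trial itself cannot establish non-inferiority. The documents do not support that: the limitation lies in the analysis text, and the planned 60 per arm gives ample power for an interval against the margin. The Primary outcome statement about 6.8 is a separate error of wording and conflicts with Sample size.

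The rates assume normal scores with SD 10. Skewed QuickDASH scores would change them but not the mismatch. Calling 6.8 the margin is an inference from the sizing, which the sponsor should confirm.

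**What to change.** **Primary outcome.** Define it as the QuickDASH score at 12 months, name 6.8 points as the non-inferiority margin (sponsor to confirm), and remove the description as a statistically significant difference.

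**Statistical analysis.** Replace the hypothesis with H0: non-operative minus ORIF ≥ 6.8. This takes higher scores as worse; the sponsor is to confirm the direction. Conclude non-inferiority only if the upper confidence limit of the difference is below 6.8, and state the level. A 90% two-sided interval matches the one-sided 0.05 behind the 27. A 95% interval would need 34 per group.

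The interval may be for the difference in means, with a robust or bootstrap method for skew. Alternatively, a Hodges–Lehmann interval keeps the stated rank method, under an explicit location-shift assumption. Covariate adjustment or a mixed model is optional.

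**Cost.** Wording in two paragraphs. At either level the overall comparison needs no extra patients; this has not been shown for treatment comparisons within age groups.

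### The protocol's only subgroup analysis compares younger with older children inside each treatment arm, so it does not estimate ORIF versus non-operative treatment by age, the question that the increase to 120 patients appears to be meant for

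*Protocol*

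**What the plan says.** The protocol's Study design section describes a "multicenter parallel-group non-inferiority randomized controlled trial (RCT"), and under Randomization "Randomization ratio is 1:1".

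The Sample size section sets the effect size and spread: "we assume clinically significant difference between the groups to be 6,8", with "the standard deviation of the QuickDASH score to be 10" points. From these it states: "With 0,05 significance level and 80% power a non-inferiority comparison would require 27 patients per group". It then adds: "Allowing a 20% dropout rate the required sample would be 30 patients per group".

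The next step enlarges the trial: "For subgroup analysis (less than 12 years vs. 12 years and over) 30 patients per age group needs to be collected". With an even age split this becomes 60 per treatment and 120 in total, that is, 30 in each of the four age-by-treatment cells.

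The Statistical analysis section names the Wilcoxon rank-sum test for the data in general and then describes the subgroup work: "Both treatment groups will be internally analyzed for differences in primary outcome regarding age (less than 12 years vs. 12 years and over"), followed by the amount of initial displacement in millimetres. No ORIF versus non-operative comparison within an age group and no treatment-by-age interaction is described. The same section allows the patient preference arm to be merged with the randomised groups.

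**The concern.** Two different questions can be asked about age.

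- **Prognosis:** among children given one treatment, do the younger and older ones end up with different QuickDASH scores? This is an observational contrast, because age is not randomised.
- **Treatment effect by age:** among children of one age group, do ORIF and non-operative treatment give different scores, and does that difference change with age? This uses the randomisation.

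The written analysis asks only the first question. A trial of two treatments enlarged for an age subgroup would normally be meant to answer the second.

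At stake is what the additional 60 patients can show. If the analysis is run as written, the report will contain an age contrast for ORIF and another for the cast group. Neither says whether non-operative treatment is non-inferior in younger or in older children. Readers may also take an age effect that is significant in one arm and not in the other as evidence that the treatment effect depends on age, which such a pair of results does not show.

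**Working it through.** **Inputs.** From the Sample size section: difference 6.8 points, SD 10, significance level 0.05 (sidedness not stated), power 80%, 27 then 30 per group, 20% dropout. From the same section: 30 per age group within each treatment, 120 in total. Assumed here: true treatment difference zero for non-inferiority, normal approximation for means (rank-sum power will differ slightly), and 24 evaluable per cell as the case where 20% of 30 are lost.

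**1. Reproduce the plan's figure.** Per group, n = 2 × SD² × (z_α + z_β)² / 6.8².

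- Non-inferiority, one-sided 0.05: 2 × 100 × (1.645 + 0.842)² / 46.24 = 26.7, so 27. This matches.
- Non-inferiority, one-sided 0.025: 2 × 100 × (1.960 + 0.842)² / 46.24 = 33.9, so 34.
- Two-sided 0.05 test of a 6.8-point difference: also 34.

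The protocol labels its 27 a non-inferiority comparison and ties the 6.8 to a difference between the groups. The 30 per cell is that block carried over: 2 treatments × 2 age groups × 30 = 120.

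**2. What 30 per cell gives the analysis as written.** For younger versus older inside one arm, SE = 10 × √(2/n) and two-sided power at 6.8 points is Φ(6.8/SE − 1.96).

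- n = 30: SE 2.58, power 75%.
- n = 24: SE 2.89, power 65%.
- 80% power needs 34 evaluable per cell.

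**3. Reading two within-arm tests side by side.** Suppose age has the same effect d in both arms, so there is no interaction. If each test has power p, exactly one is significant with probability 2p(1 − p), which cannot exceed 50%. With 30 per cell and SD 10:

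| Assumed d (points) | p | Exactly one significant |
|---|---|---|
| 2 | 0.118 | 21% |
| 5 | 0.491 | 50% |
| 6.8 | 0.750 | 38% |
| 8 | 0.873 | 22% |

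At 6.8 points with 24 per cell, p = 0.654 and the figure is 45%. The protocol gives no age effect, so the range is the result, not any one row.

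**4. What 120 patients give the treatment question.**

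- ORIF versus non-operative within one age group, non-inferiority at 6.8, one-sided 0.05: power = Φ(6.8/SE − 1.645) = Φ(2.634 − 1.645) = 84% with 30 evaluable per cell, and Φ(2.356 − 1.645) = 76% with 24.
- Treatment-by-age interaction: SE = 10 × √(4/n) = 3.65 (n = 30) or 4.08 (n = 24). Two-sided 0.05 power at 6.8 points is 46% or 38%. The difference detectable with 80% power is 2.80 × SE = 10.2 or 11.4 points. For 6.8 points, 80% power needs 4 × 100 × 2.80² / 46.24, about 68 evaluable per cell, or 272 in total.

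**The case against.** The best counter-argument is textual. The Sample size section never says that the age subgroup analysis compares treatments. Taken literally, younger versus older with 30 per age group in each arm is exactly the contrast that the Statistical analysis section describes, and the two sections would then agree. The arithmetic alone does not refute this, since a one-sided 0.05 younger-versus-older test of 6.8 points would give the same 27. What favours the treatment reading is that the protocol derives 27 as a non-inferiority comparison between the groups, and a non-inferiority margin has no natural meaning for younger against older children. The link is therefore an inference. The literal reading does not rescue the plan either: a two-sided within-arm test would be undersized (34 needed), and it would still say nothing about the treatment effect.

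A reader might infer more than the documents support, on four points.

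- **The extra 60 patients are wasted.** They are not. All 120 serve the overall comparison of treatments.
- **The sample size was also set for displacement.** It was not. The sizing names age only.
- **The investigators plan to claim effect modification from two within-arm p-values.** Nothing says so. That is a risk in how the results are read, and prognostic analysis is a legitimate secondary aim.
- **The rank-sum test is misapplied to displacement in millimetres.** The rank-sum sentence is general and the subgroup paragraph names no test. How displacement is grouped or modelled can be left to an SAP, which is not shown.

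The absence of an interaction model could also be left to an SAP. What is not mere omission is that the protocol commits itself to a subgroup analysis, and the one it describes does not address treatment effect by age.

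**Conclusion.** The point holds. The stated subgroup analysis estimates age and displacement as prognostic factors within each treatment. It does not estimate ORIF versus non-operative treatment within an age group or test whether that effect differs by age. That much follows directly from the text.

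That the increase from 60 to 120 was meant for a treatment comparison by age is a well-supported inference, limited to age. The risk of a misleading pair of within-arm results is roughly 20 to 50% under assumed equal age effects of 2 to 8 points, 30 per cell and SD 10, and never above 50%.

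The planned sample can nearly deliver non-inferiority within each age group at the one-sided 0.05 level that reproduces the plan's 27. It cannot deliver a firm interaction test at 6.8 points. The overall comparison is untouched, so this is a change that should be made rather than a flaw in the primary analysis.

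**What to change.** Replace the subgroup sentence in the Statistical analysis section with wording such as:

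> In randomised patients, the ORIF minus non-operative difference in 12-month QuickDASH is estimated within each age group (<12, ≥12 years) with a confidence interval at the level matching the sample-size calculation (two-sided 90% for one-sided 0.05) and compared with the 6.8 margin. Treatment-by-age-group and treatment-by-displacement (mm, continuous) interactions are exploratory. Within-arm comparisons by age or displacement are descriptive only.

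In the Sample size section, say that the age subgroup analysis is a comparison of treatments within each age group, if that is the intention. State its power at both evaluable sizes derived above, and that the age interaction can detect only about 10 to 11 points with 80% power. The restriction to randomised patients matters because the plan otherwise allows the preference arm to be merged.

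The cost is a small amount of extra analysis and a less favourable stated subgroup power. No new data or patients are needed.

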### **Inclusion criteria:**

Patients aged 7-16 years presenting with a  $\geq 2$ mm displaced non-incarcerated medial epicondyle fracture with or without concomitant elbow dislocation and normal ulnar nerve function.

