## **Baseline**

Standard anterior-posterior and lateral radiographs of the elbow will be obtained after closed reduction of the possible elbow dislocation. All participants in either the RCT or patient's choice arm undergo cone-beam or normal computer tomography (CT) before treatment initiation. Initial fracture dislocation will be calculated from the CT scans in three planes (anterior-posterior, cranial-caudal and medial-lateral) and both radiographs (anterior-posterior and lateral) using the method described by Edmonds et al (2010). Date of injury, method of injury, patient's age at time of injury, sex, injured side, dominant hand and main sport or musical instrument as well as level will be documented. Motor and sensory function as well as range of motion of both upper limbs will be assessed. Carrying angle (degrees) and valgus stress test will be assessed if possible for both limbs.

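### The protocol names only an under-12 versus 12-and-over age analysis; if the age effect is gradual, the cut loses about 24–36% of the age information, and a continuous-age model should be added beside it

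*Protocol*

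**What the plan says.** The Baseline section lists among the recorded items "age at time of injury, sex, injured side", together with the date of injury. The Inclusion criteria give the range: "Patients aged 7-16 years presenting with a" displaced fracture of the kind under study.

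The Statistical analysis section plans a comparison inside each treatment group, on the primary outcome, by "age (less than 12 years vs. 12 years and over) at time of injury". The same sentence also names initial displacement in millimetres, without a cut-point.

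The Sample size section uses the same two age groups: "For subgroup analysis (less than 12 years vs. 12 years and over) 30 patients per age group needs to be collected". It continues, "Assuming 50-50 split in the patients between the age groups", and arrives at 60 per treatment and 120 in total. No section explains why 12 was chosen, and no other form of age analysis is named.

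**The concern.** A two-group split treats a child of 7 like one of 11, and treats children of 11.9 and 12.1 as different. If the outcome, or the ORIF versus non-operative difference, drifts gradually with age, the split uses only part of what the trial has already recorded. A real trend is then easier to miss, and a non-significant split could be reported as showing that age does not matter.

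The split is a stated rule, so this is not a matter of detail left to an analysis plan that is not shown.

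**Working it through.** **Inputs from the protocol.** Ages 7–16, a 50:50 split at 12, SD 10, a difference of 6.8 points, 60 per treatment and 20% dropout. This gives 60 × 0.8 = 48 evaluable per arm and 24 per age-by-treatment cell.

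**Assumptions not in the protocol.** The age distribution within 7–16, and the shape of the age effect.

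**The protocol's own figures.** The 27 per group reproduces with one-sided 0.05: 2 × (1.645 + 0.842)² × 10² / 6.8² = 26.7, rounded up to 27. The total also follows: 30 per age group × 2 age groups × 2 treatments = 120. (The step from 27 to 30 does not match a 20% dropout, since 27 / 0.8 = 34 after rounding up. That is a separate matter and does not enter here.)

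**Information kept by the cut.** For an effect linear in age, the share kept is the squared correlation between age and the indicator of being 12 or over: p(1 − p) × (difference in mean age)² / variance of age.

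- Evenly spread from 7 to under 17: 0.25 × 5² / (100/12) = 6.25 / 8.33 = 0.75, a loss of 25%.
- Whole years 7 to 16 in equal numbers: 6.25 / 8.25 = 0.758, a loss of 24%. The result therefore does not depend on age being recorded finely.
- Evenly spread from 7 to 16.0: (4/9)(5/9) × 4.5² / 6.75 = 0.741, a loss of 26%.
- Bunched around 12 (truncated normal, mean 11.5–12.5, SD 2–3; or triangular): 0.65–0.69 kept, a loss of 31–35%.
- Limit for a normal distribution cut at its median: 2/π = 0.637, a loss of 36%.

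**Within-arm power.** Simulated with 48 per arm, SD 10, ages even over 7 to under 17 and two-sided 0.05. The linear slope is 1.36 points per year, which puts 1.36 × 5 = 6.8 points between the two age-group means. The step is 6.8 points at 12.

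| True age effect | Rank-sum on split | Rank correlation with age | Linear term |
|---|---|---|---|
| Linear, 1.36 per year | 58% | 71% | 75% |
| Step of 6.8 at age 12 | 60% | 48% | 50% |

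The like-for-like comparison in the first row is 58% against 71%, because both are rank methods. The last few points come from using a parametric test. If the whole change occurs between 11 and 13, all three tests have power of about one half.

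**Treatment-by-age interaction.** With 48 per arm and slopes differing by 2.02 points per year, power is about 67% on the split and 80% on continuous age. That is a large effect: 2.02 × 10 = 20 points across the range. For a 6.8-point difference between the two age groups' treatment effects, the normal approximation at 24 per cell gives 6.8 / (10 × √(4/24)) = 1.67, or 38% power. With continuous age and a linear truth it gives 1.67 / √0.75 = 1.92, or 49%. At 30 per cell the figures are 46% and 58%.

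**The case against.** The strongest objection is that continuous age wins only if the truth is gradual. Nothing in the protocol favours a linear trend over a threshold, and the second row of the table shows the split ahead by about 10 points when there is a step at 12. This stands. It rules out replacing the split, but not adding to it.

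A reader might infer that the analysis which doubled the trial throws away a quarter of its information. The documents do not support that. The Sample size section repeats the treatment-group size in each age group, so that "the sample size would be 60 per ORIF and non-operated equaling a total of 120 patients". Those numbers suit an ORIF versus non-operative comparison within each age group, and the squared correlation of 0.75 says nothing about information lost there. The loss applies to the within-arm age comparison in the Statistical analysis section, and to any test of whether the treatment difference changes with age.

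It is also fair to object that the illustrated effects are large. A slope of 1.36 per year is 13.6 points from 7 to 17, twice the 6.8 that the protocol calls clinically significant. For a smaller interaction both methods are underpowered, so the added model reduces the risk of a falsely reassuring null result without removing it.

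Finally, a prespecified two-group analysis is not an error in itself, and a fuller analysis plan could add continuous age. That is so, but the protocol as written names the split and nothing else.

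**Conclusion.** The point holds conditionally. If the outcome or the treatment difference changes roughly linearly over 7–16 years, the split loses 25% of the age information for evenly spread ages, and about 24–36% across plausible age distributions. At 25%, the 96 evaluable children carry the age information of 96 × 0.75 = 72. With a true step at 12 the loss is zero and the split is preferable.

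A flat loss of a quarter, stated without these conditions, would go too far: the protocol gives neither an age distribution beyond the range and the 50:50 assumption, nor a shape for the age effect. The primary treatment comparison is untouched. This is a low-severity improvement to a secondary analysis.

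**What to change.** In the Statistical analysis section, keep the under-12 versus 12-and-over analysis and add one prespecified model of 12-month QuickDASH with treatment, age at injury in years and their interaction. Report the fitted ORIF versus non-operative difference with its confidence interval across 7–16 years. State that absence of an age difference will not be concluded from a non-significant split alone, and present the interaction estimate with its interval because power for it is limited. If there is a reason to expect a threshold at 12, say so in one sentence.

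The cost is one extra model on data already collected, with no new patients or visits. The downsides are an assumed smooth (here linear) age trend, which the retained split helps to check, and one more secondary test. Keeping the split also means that the age groups provided for in the Sample size section still serve the analysis for which they were sized.
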